#### Secondary outcomes—investigating the mechanisms influencing behaviour change

##### Internal and external resilience

The 25-item Connor-Davidson CD-25 scale measures the internal resilience construct of the psychosocial model of resilience. [43] Connor and Davidson [43] found evidence for the convergent validity of the scale and observed satisfactory internal consistency (α = 0.89) in the general population and satisfactory test–retest reliability (intraclass coefficient = 0.87) in a clinical sample.

The 7-item ENRICHD Social Support Inventory [44] will be used to measure self-reported external resilience. Mitchell [44] found evidence of convergent validity and observed satisfactory internal consistency (⍺ = 0.86). Vaglio et al. [49] observed satisfactory test–retest reliability over a one-month interval (intraclass correlation = 0.94).

##### Self-efficacy

The Smoking Abstinence Self-Efficacy Questionnaire [50] will be used to measure confidence in the ability to change smoking behaviour. Total scores range from 0 to 24, with higher scores indicating greater self-efficacy. Spek et al. [50] observed that the questionnaire had good internal consistency in their sample (α = 0.89) and found evidence for predictive validity.

##### Motivation

Participants’ level of motivation to quit smoking will be measured with Biener and Abrams Contemplation Ladder. [51] This test represents a ladder with ten rungs and five verbal anchors evenly dispersed. Participants select a number from 0 (no thought of quitting) to 10 (taking action to quit). Ladder scores were found to be correlated with the number of previous quit attempts, thereby illustrating construct validity.

##### Stress

The Perceived Stress Scale-10 is a 10-item self-report questionnaire. [52] Lee [53] reviewed the psychometric properties of the scale, finding that all 12 included studies indicated sufficient internal consistency (α > 0.70). Several studies have found evidence for convergent validity. [54, 55]

##### Nicotine dependence

We will assess nicotine dependence with the Fagerstrom Test for Nicotine Dependence, a short, six-item self-report questionnaire. [56] A review of the psychometric properties of the test found excellent test–retest reliability over a range of time periods. [57] Internal consistency was found to be moderate, with ⍺ ranging from 0.55 to 0.74 across 14 studies. Construct validity is evinced by moderate to strong correlations with biological markers of nicotine.

##### Goal achievement

The Problems and Goals Assessment Scale will be administered to SRG participants to measure progress towards goals. [58] The scale consists of a semi-structured evaluation designed to identify what the participant sees as their main problem, its impact, and how it makes them feel. The person rates the degree to which they view this as a problem on a 9-point scale ranging from “not at all” (0) to “a lot” (8). After goals are set to ameliorate the problem, achievement towards the goals is also assessed on a 9-point scale, ranging from “no success” (0) to “complete success” (8). Goal attainment scaling methods are idiosyncratic because they measure an individualised outcome, but their reliability and validity is supported by an extensive literature base. [59]

##### Equanimity

We will use the Equanimity Scale-16 to measure equanimity, which refers to a non-reactive attitude towards experience and is thought to be a key mechanism of action in mindfulness-based interventions. [60] Only participants in the MT and MiCBT arms will be administered the scale. Evidence was found for convergent and divergent validity, and satisfactory internal consistency (⍺ = 0.88) and test–retest reliability (r = 0.87) over a two-to-six-week period was observed. [60]

##### Quality of life

We will measure quality of life with the EQ-5D-5L [61] to assist in estimating the cost-effectiveness of the interventions. The questionnaire comprises a visual analogue scale assessing general health in addition to a 5-component scale including mobility, self-care, usual activities, pain/discomfort, and anxiety/depression. A systematic review found evidence for good reliability and validity across a range of populations. [62] The responses to the 5-component scale questions will be converted to utility scores using an algorithm that reflects Australian population values, noting tariffs for the EQ-5D-5L instrument are in development, but should be available by the time of data analysis. Utility scores are bounded at 1, representing best imaginable health, with a value of zero representing health states that are equivalent to being dead (negative values are possible, representing health states that are determined to be worse than being dead).

#### Costs-effectiveness

Any intervention effects on smoking cessation were not anticipated to lead to differences in health care use (e.g., GP visits, hospitalisations, etc.) between the control and intervention groups over the time horizon of the clinical trial. The lack of an expected effect on health care use did not justify the additional burden of collecting resource use and cost data from participants.

A trial-based economic evaluation will estimate intervention costs, in total, per intervention group participant, per additional intervention group participant demonstrating smoking cessation and per mean change on the EQ5D-5L quality of life instrument. If significant differences in smoking cessation rates are observed, external data describing the long-term health benefits and health care cost impacts will be sought to inform modelled estimates of downstream cost, mortality, and quality of life effects. These data will inform the estimation of the incremental cost per QALY gained.

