**Methods:**

We plan a four-arm parallel 12-month RCT with a 6-month follow-up to test the efficacy of three group-based interventions each followed by peer support. Arm 1: mindfulness-integrated cognitive behavioural therapy; Arm 2: mindfulness training; Arm 3: setting realistic goals; Arm 4: active control group directed to quit services. All interventions will be administered online. Participants are adult smokers in Australia (N = 812) who have an average weekly household income less than $457AUD or receive welfare benefits. Group-based interventions will occur over 6 months, followed by 6 months of forum-based peer support. Primary outcome: self-reported 14-day period prevalence of smoking abstinence at 6 months, with remote biochemical verification of saliva cotinine (< 30 ng/mL). Secondary outcomes include: internal resilience (Connor-Davidson Resilience Scale-25); external resilience (ENRICHD social support tool); quality adjusted life years (EQ-5D-5L); self-efficacy for smoking abstinence (Smoking-Abstinence Self-Efficacy Questionnaire); motivation to quit smoking (Biener and Abrams Contemplation Ladder); nicotine dependence (Fagerstrom Test for Nicotine Dependency); equanimity (Equanimity Scale-16); stress (Perceived Stress Scale-10); goal assessment/attainment (Problems and Goals Assessment Scale).

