## Methods

The following protocol (version 5, September 9th 2022) follows SPIRIT guidelines for reporting protocols (see Additional file 1). In this four-arm parallel-group RCT of SRG, MT and MiCBT versus an active control (equal allocation ratio), we will deliver the interventions to small groups of smokers to maximise the potential cost-effectiveness. 6-months of these interventions will be followed by 6-months of online peer support and a further 6-month follow-up period. The control group will be directed to optional resources including counselling (Quitline) and information about pharmacological aid. We aim to: (a) test the efficacy of the three interventions (SRG, MT and MiCBT) for smoking cessation and (b) levels of resilience in low SES groups and how this changes during exposure to the interventions, (c) measure the cost-effectiveness and cost-utility of the interventions in low SES groups, and (d) undertake a process evaluation of the different interventions in low SES groups. We hypothesise the following:H1: The proportion of participants who report 14-day period abstinence from smoking at 6 months will be significantly higher for each intervention group compared to the control group.H2: Amongst participants that report 14-day period abstinence at 6 months, the proportion of participants who report 14-day period abstinence at 12 months will be significantly higher for each intervention group compared to the control group.H3: The proportion of participants who report 14-day period prevalence abstinence from smoking at 6 months post-trial (18 months from baseline) will be significantly higher for each intervention group compared to the control group.H4: Levels of resilience measured by the Connor-Davidson CD-25 [43] and ENRICHD Social Support Inventory [44] will be significantly higher for each intervention group compared to the control group at 6, 12 and 18 months post randomisation.H5: The interventions will improve smoking cessation and QALYs at a reasonable and acceptable incremental cost.

In addition, we pose the following research questions for the qualitative component of the study (that pertains to the process evaluation):RQ1: Have the different interventions been implemented and received as intended?RQ2: What are the barriers and facilitators associated with the first research question?RQ3: For whom, and in what circumstance were the interventions effective (and cost-effective) or not, and why?

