#### Cost-effectiveness

A cost-effectiveness model will be used to estimate all important differences in costs and benefits between the three trial arms if there is significant uncertainty regarding the most cost-effective option based on the within trial analysis. Published smoking cost-effectiveness models will be reviewed to identify the most valid available model from an Australian perspective, which will be used to estimate the lifetime incremental costs and QALY gains associated with smoking cessation, as applied in previous economic evaluations of smoking cessation interventions.

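### The trial-based evaluation divides cost by mean change on the EQ-5D-5L, so the trial-measured QALYs named in the abstract are never derived, and cost per QALY comes only from conditional modelling

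*Protocol article*

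**What the plan says.** Three places set up a QALY outcome:

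- The Methods part of the abstract lists "quality adjusted life years (EQ-5D-5L" (closing bracket cut here) among the secondary outcomes.
- Aim (c) in Methods is to "measure the cost-effectiveness and cost-utility of the interventions in low SES groups". QALYs are implied there, not named.
- H5 in Methods reads "The interventions will improve smoking cessation and QALYs at a reasonable and acceptable incremental cost".

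Under Measures, Quality of life, the first step is given: "The responses to the 5-component scale questions will be converted to utility scores using an algorithm that reflects Australian population values". The section goes no further than utilities.

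Under Measures, Costs-effectiveness, the trial-based evaluation gives intervention costs in total, per participant, and "per additional intervention group participant demonstrating smoking cessation and per mean change on the EQ5D-5L quality of life instrument". A cost per QALY comes only in the next step, which is conditional: "If significant differences in smoking cessation rates are observed, external data describing the long-term health benefits and health care cost impacts will be sought". Of those external data and the modelling they support, the section says "These data will inform the estimation of the incremental cost per QALY gained".

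Under Statistical analysis, Cost-effectiveness, a published model is to give lifetime costs and QALY gains, on a different condition: "if there is significant uncertainty regarding the most cost-effective option based on the within trial analysis".

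**The concern.** A QALY is utility multiplied by time. A mean change on the instrument is a difference in score with no duration attached. Cost per mean change therefore cannot be read as cost per QALY or set against a cost-per-QALY threshold, and it does not deliver the secondary outcome in the abstract.

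Timing matters in this design: 6 months of group sessions, 6 months of peer support, then 6 months of data collection only. An effect could come early and fade, or build slowly. A measure without time treats such patterns alike, or misses one of them.

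The modelled QALYs do not fill the gap. They are driven by cessation and rest on external data or a published model. The interventions aim at resilience, and stress is among the outcomes, so utility could move without quitting. A cessation-driven model would not register that, although the trial collects the data that could.

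**Working it through.** **1. Follow the EQ-5D-5L data through the document.** Responses become utilities (Quality of life). The only within-trial economic use then stated is the mean-change ratio (Costs-effectiveness). No section takes the trial's utilities to QALYs. Both routes to a QALY are modelled, and their triggers differ: significant cessation differences in one section, significant uncertainty after the within-trial analysis in the other. Either condition can hold without the other.

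**2. Illustrate what the missing time dimension does.** The plan gives no figure for the economic outcome, so there is none to reproduce. All inputs here are assumptions: EQ-5D-5L visits at 0, 6, 12 and 18 months (the schedule is in Table 1, which is not shown), the utility differences from control in the table, and an incremental cost of $500 per participant. Change is taken, for now, as baseline to month 18.

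Trapezium rule with intervals of 0.5 year, d being the utility difference at each visit:

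QALY difference = 0.5 × [(d0 + d18)/2 + d6 + d12]

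| Path | d at 0, 6, 12, 18 | Change at 18 | Cost per unit change | QALY difference | Cost per QALY |
|---|---|---|---|---|---|
| Early, held | 0, 0.03, 0.03, 0.03 | 0.03 | $16,667 | 0.5 × (0.015 + 0.06) = 0.0375 | $13,333 |
| Linear | 0, 0.01, 0.02, 0.03 | 0.03 | $16,667 | 0.5 × (0.015 + 0.03) = 0.0225 | $22,222 |
| Late | 0, 0, 0, 0.03 | 0.03 | $16,667 | 0.5 × 0.015 = 0.0075 | $66,667 |
| Transient | 0, 0.03, 0.03, 0 | 0 | undefined | 0.5 × 0.06 = 0.030 | $16,667 |

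The first three paths share one ratio, while their QALY gains differ by 0.0375/0.0075 = 5 times.

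**3. Vary the assumed visits.** At 0, 3, 6, 9, 12 and 18 months, a gain held from month 3 is worth 0.25 × 0.015 + 3 × 0.25 × 0.03 + 0.5 × 0.03 = 0.04125 QALY, or $500/0.04125 = $12,121 per QALY. The linear and late paths stay at 0.0225 and 0.0075.

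**4. Vary the reading of mean change.** Suppose it means the average change over the visits at 6, 12 and 18 months. The four paths give 0.03, 0.02, 0.01 and 0.02. The transient path is no longer zero. But the linear and transient paths now share $500/0.02 = $25,000 per unit change, while their costs per QALY are $22,222 and $16,667. This reading is closer to a QALY but still not one.

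**5. How often the first trigger might fail.** The section on sample size plans 80% power for 25.2% against 13.6%. With p̄ = 0.194, n = [1.960 × √(2 × 0.194 × 0.806) + 0.842 × √(0.252 × 0.748 + 0.136 × 0.864)]² / 0.116² ≈ 181.2, so 182 per group, as stated. Even if those rates are true, a given comparison misses significance in about 1 − 0.80 = 20% of trials, before any multiplicity adjustment. If no comparison is significant, the Measures section offers no cost per QALY.

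**The case against.** The strongest reply is that this is a coherent two-step design: short-term ratios in natural units within the trial, then lifetime QALYs by modelling. The document expects no difference in health care use over the trial horizon and looks to long-term data for mortality and quality-of-life effects. Neither H5 nor aim (c) sets a horizon, so modelled QALYs are a legitimate, if conditional, route to both. This stands. A reader might infer that the plan cannot address H5 or aim (c) in QALY terms at all; the lifetime model under Statistical analysis means the document does not support that.

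A second reply is that an article may leave the QALY calculation to a health-economics or analysis plan. That would answer an omission. Here the article names a different quantity as the denominator, so the mismatch is in what it states.

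Third, mean change is not defined as baseline to month 18. This is right, and a reader might wrongly take the zero for a fading gain as a consequence of the plan. It follows only under that reading (step 4). The wording also leaves open whether the change is relative to control, and whether it concerns the utility or the visual analogue scale, both of which the instrument yields.

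Fourth, one might infer that a change score ignores chance imbalance in baseline utility. It does not, since baseline is subtracted. It can over-correct through regression to the mean, which is a reason to prefer regression on baseline, but a secondary one.

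Finally, a within-trial QALY difference will probably be small and imprecise. That is true and should show in its interval; it does not turn a mean change into a QALY.

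**Conclusion.** The point holds in a limited form. The abstract's QALY outcome from the EQ-5D-5L has no derivation within the trial, because the stated ratio uses a quantity without time. Cost per QALY depends on modelling whose two stated triggers disagree, and under the Measures section it lapses if cessation does not differ significantly.

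The dollar figures show only that a change score does not track QALYs. Visits, utility differences and cost are all assumed, so they are not estimates for this trial, and they do not show that its arms would be ranked wrongly. The primary outcome, sample size and efficacy inference are unaffected. The change is worth making because the mismatch is explicit and cheap to correct.

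**What to change.** In Measures, Costs-effectiveness, replace the mean-change denominator with incremental cost per QALY gained over trial follow-up. Then:

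- derive each participant's QALYs as the area under the EQ-5D-5L utility curve across all scheduled EQ-5D-5L visits, with the horizon matched to Table 1;
- compare each intervention with control by regression adjusting for baseline utility;
- report the result with its uncertainty, whatever the cessation result;
- keep the lifetime model as an extension, and state one trigger for it in both cost-effectiveness sections.

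The cost is a few sentences and a few lines of analysis code, using EQ-5D-5L and intervention-cost data already planned. Whether the scheduled visits are frequent enough for a good area under the curve should be checked against Table 1. The downside is that the within-trial QALY difference will probably be small and its interval wide.

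### Two sections set different, unreconciled conditions for the modelled cost-per-QALY analysis, and one of them counts three arms in a four-arm trial

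*Protocol article*

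**What the plan says.** The opening of Methods describes a four-arm trial, three interventions against an active control. It states aim (c), cost-effectiveness and cost-utility, and H5, improved cessation and QALYs at acceptable incremental cost, without any condition.

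Costs-effectiveness (under Measures) first commits to a trial-based evaluation: intervention cost in total, per participant, per additional quitter and per mean change on the EQ-5D-5L. This part is unconditional. The section then adds: "If significant differences in smoking cessation rates are observed, external data describing the long-term health benefits and health care cost impacts will be sought". Their purpose is to project later costs, deaths and quality of life. It closes: "These data will inform the estimation of the incremental cost per QALY gained".

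Cost-effectiveness (under Statistical analysis) says a model will be used to "estimate all important differences in costs and benefits between the three trial arms", but only "if there is significant uncertainty regarding the most cost-effective option based on the within trial analysis". A published model will be chosen, "which will be used to estimate the lifetime incremental costs and QALY gains associated with smoking cessation".

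**The concern.** Both sections lead to the same kind of result, lifetime incremental costs and QALYs from external evidence, but each opens the door on a different condition. The first is a significance test on cessation, with no contrast, time point or alpha named. The second is uncertainty about which option is most cost-effective. The text does not say whether either condition is enough, whether both are needed, or whether one section takes precedence.

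Three things are at stake. The decision to produce the modelled cost per QALY could be made after the results are seen, by choosing which section to follow. A stated aim could be left partly unanswered. And if the significance condition is followed, the model is run only on cessation effects that were large enough to pass a test, which overstates them on average. A cost-effectiveness decision rests on expected costs and QALYs with their uncertainty, and a non-significant cessation difference does not remove the need for that estimate.

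Separately, the reference to three arms does not fit the design. If the omitted arm were the control, the model would have no comparator for incremental cost.

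**Working it through.** **Step 1. The two conditions side by side.** Write A for significant cessation differences (Measures) and B for significant uncertainty about the most cost-effective option (Statistical analysis).

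| Cessation | Ranking after within-trial analysis | Under A | Under B |
|---|---|---|---|
| Significant | Uncertain | model | model |
| Significant | Clear | model | no model |
| Not significant | Uncertain | no model | model |
| Not significant | Clear | no model | no model |

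The sections conflict in rows 2 and 3 and agree in rows 1 and 4. If both conditions are needed, the model runs only in row 1; if either is enough, it runs in rows 1 to 3.

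All four rows can occur. For row 1, two interventions may both beat control and yet be hard to rank: with assumed rates of 25.2% and 20.0%, power between two active arms at 182 each is only 22%. For row 4, interventions that add cost and almost no quitters may leave control clearly the best value.

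**Step 2. Reproduce the sample size** (Sample size and power analysis). Inputs: rates 13.6% and 25.2%, two-sided alpha 0.05, power 80%, 10% drop-out.

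- Difference d = 0.252 − 0.136 = 0.116; mean rate 0.194.
- Pooled term √(2 × 0.194 × 0.806) = 0.5592; unpooled term √(0.136 × 0.864 + 0.252 × 0.748) = 0.5532.
- n = [(1.960 × 0.5592 + 0.8416 × 0.5532) / 0.116]² = 181.2, so 182.
- 182 / 0.9 = 202.2, so 203; 4 × 203 = 812.

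The stated 182, 203 and 812 all reproduce.

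**Step 3. How often condition A fails for one named comparison.** Power = Φ[(d√n − z × 0.5592) / 0.5532], with d√n = 0.116 × √182 = 1.5649.

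- Alpha 0.05 (z = 1.960): (1.5649 − 1.0961) / 0.5532 = 0.848; power 80.2%; miss about 20%.
- Alpha 0.0167 (z = 2.394; the level the Analyses section gives for testing at 6, 12 and 18 months): (1.5649 − 1.3388) / 0.5532 = 0.409; power 65.9%; miss about 34%.

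**Step 4. How often no comparison is significant.** The wording of A may instead be met by any one of the three comparisons. Simulated with 182 per arm, shared control at 13.6% and pooled z-tests:

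| True intervention rates | None significant, alpha 0.05 | None significant, alpha 0.0167 |
|---|---|---|
| All three 25.2% | about 5% | about 12% |
| One at 25.2%, two at 13.6% | about 16% | about 32% |
| All three 20% (assumed, not a protocol figure) | about 38% | about 59% |

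**Step 5. Selection.** In simulations of one comparison with a true difference of 11.6 points, the mean observed difference among significant results was about 13.0 points at alpha 0.05 and 13.8 at 0.0167. A model run only after significance would take in effects overstated by roughly 1.4 to 2.2 points on average.

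**The case against.** The best reply is that little of the economic plan depends on these conditions. The trial-based evaluation is carried out whatever the p-value, and the protocol states that EQ-5D-5L responses will be converted to utilities, so a cost-effectiveness result and a utility-based ratio will exist in any case. This stands, and it confines the point to the modelled cost per QALY.

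A reader might infer that the two conditions are opposites, so that whenever one section says no the other says yes. The documents do not support that: the conditions concern different quantities and can hold or fail together. It follows that the miss rates in the working are not rates of conflict; a non-significant cessation result does not by itself trigger the second section.

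The miss rates for one named comparison are also the less favourable reading, because the first section names no contrast. If any comparison counts and all three interventions work as planned, the condition fails in only about 5% or 12% of trials.

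Finally, the three-arm wording is probably a slip for the three interventions. The same section speaks of incremental costs, which presuppose a comparator, and nothing says that control is excluded. That is fair, but the correction is one word and the literal text is wrong.

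**Conclusion.** The point stands in a limited form. The two sections give different rules for the same modelled analysis, and they lead to different decisions in two of the four possible situations. The arm count contradicts the design. Under the significance condition, the modelled part of aim (c) and H5 would go unanswered in somewhere between about 5% and 34% of trials in which at least one intervention has the full planned effect, depending on alpha, on how many interventions work and on whether one named comparison or any comparison counts. With a smaller true effect the share is larger. These figures assume 182 analysed per arm and simple two-group tests. Severity is minor to moderate: the analysis is secondary and the primary outcome is untouched.

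A reader might also infer that incremental cost is biased because collecting participants' resource use was judged not worthwhile (the expected lack of effect "did not justify the additional burden of collecting resource use and cost data from participants"), which leaves use of Quitline, nicotine replacement and stop-smoking medicines uncosted. The documents do not carry this. Phase 1 offers the same Ask, Advise, Help referral to every arm, bias would need uptake to differ by arm, and no figure on uptake is given. It is not part of this point.

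**What to change.** Put one rule in both sections: the modelled incremental cost per QALY is estimated for all four arms, with the active control as comparator, whatever the significance of the cessation result, and the uncertainty in the estimated quit rates is carried through to the final estimate. Delete both conditions, and change three to four in the Statistical analysis section.

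The cost is a change of wording plus modelling work that at present is planned only under some outcomes. No new data from participants are needed.
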